## 4. Potential Challenges and Limitations

DOT does not provide information on the subcortical structures; only connectivity between different regions of the cerebral grey matter is measured. Hypoxic–ischemic brain injury may affect the microstructure of the white matter tracts and deep grey matter. Structural connectivity between brain regions is better assessed by diffusion tensor MR imaging. Our results will not provide information about the deep grey matter structures such as the basal ganglia and thalamus. Future multi-modal approaches, such as DOT combined with EEG and MRI, may overcome the challenge of individual modality limitations. The limitation of most pediatric optical systems is the inability to place a full array of optical probes just as in adults. In adults, high-density DOT (64 channels on each side) achieves improved spatial resolution and better separation of cerebral signals from superficial confounds. The translation of high-density DOT techniques to neonates is a challenging task. There is a need for cap ergonomics to maximize comfort while enhancing the coupling between the optical probes and the infant’s scalp. Since this is a feasibility study, we initially planned to start with 27 channels. If acceptable signal quality is not achieved, we may try (a) increasing the number of optodes used or (b) using subject-specific structural MRIs to validate the individualized DOT reconstructions relative to subject-matched MRI. Combining atlas transformation techniques with age-matched neonatal templates could provide realistic head models using a nonlinear warping procedure.

The small sample size may provide a false sense of any association between functional connectivity and prognostication in neonates with HIE. Given the nature of HIE and the sensitivity of such discussions with parents, a challenge that may arise during this study is obtaining informed consent from parents and substitute decision makers during a time when the prognosis of their baby is uncertain. Many parents may not want to discuss any intervention that will not benefit their baby. As participants are recruited, it will be determined whether our approach to the consent process needs to be altered to have respectful conversations with parents.

## 5. Discussion

This study examines the potential for more accurate neurocognitive prediction methods in the early neonatal period to inform clinical decision making and early intervention. The opportunity for DOT to assess functional connections between brain regions and quantify region-specific brain activity at the bedside could open up many doors for functional prognostication in HIE. However, the feasibility of such a study needs to be assessed before conducting a clinical trial to evaluate this new technology. Additionally, it is essential to understand the relationship between resting-state functional connectivity measures, assessed via DOT, and neurological outcomes. Given the prevalence of HIE and its sequelae, determining if DOT can be used to prognosticate neurological outcomes would have significant implications for future neonatal care. Another future direction for this study would be to add EEG electrodes to the DOT caps and record fNIRS and EEG simultaneously. Quantitative EEG abnormalities in this cohort of neonates are being explored for prognostic utility [54]. Since EEG allows for source localization, including during sleep, combining these two methodologies could facilitate further localization of cerebral oxygenation during sleep–wake cycles [55].

## 6. Conclusions

Perinatal brain injury is a complex condition in neonates associated with significant future implications for neurological function in later childhood. There is a need for more effective prognostic tools that can help clinicians identify changes in brain function in the early stages of life, enabling the development of tailored early intervention strategies to improve future outcomes. This study investigates the potential clinical use of a non-invasive bedside tool that can provide additional information about the injured neonatal brain, complementing the information from structural neuroimages.

## Figures and Tables

**Figure 1 neurosci-06-00060-f001:**
[figure not shown]
Study enrollment flow diagram.

**Figure 2 neurosci-06-00060-f002:**
[figure not shown]
(**a**) The experimental setup showing the neonatal cap with sensors attached placed on a mannequin, along with two fNIRS devices and the Laptop that is used for remote monitoring. (**b**) An illustration of the device being used in the NICU bedside. A Bluetooth-enabled system with a low footprint can be comfortably brought to the NICU bedside.

**Figure 3 neurosci-06-00060-f003:**
[figure not shown]
Customized neonatal caps with and without the optode. The fabric used for the cap is 5% spandex and 95% cotton knit. The soft rubber optodes ensure the cap is gentle on the neonatal scalp (**A**). The optodes are slid into the holders until they are flush with the holders, which ensures good contact with the neonatal scalp (**B**).

**Figure 4 neurosci-06-00060-f004:**
[figure not shown]
Representation of the two-dimensional layout of the optodes on the scalp. Yellow optodes represent the transmitters (optodes that emit the near-infrared light), and the blue optodes represent the receivers (optodes that detect the light scattered through the cortex and back). Small white-grey dots represent the channels between each transmitter and receiver pair (optical paths where the fluctuations in near-infrared light are measured). F, T, P, C, and O refer to the anatomical landmarks (frontal, temporal, parietal, central, and occipital, respectively) according to the 10–20 electrode placement system.

**Figure 5 neurosci-06-00060-f005:**
[figure not shown]
Demonstration of the principle of DOT, which uses differing absorption of infrared light by deoxygenated and oxygenated hemoglobin to measure changes in cortical blood flow in accordance with the Beer–Lambert Law.

**Table 1 neurosci-06-00060-t001:** Summary of the study objectives, outcomes, and analysis plans.

Objectives	Outcomes	Criteria for Success	Method of Analysis
Primary Aims			
Assess the feasibility of recruitment and retention strategies and data collection methods in the NICU.	Recruitment and retention rates, missing data.	(i) 80% of the eligible patients consent to the testing; (ii) 90% of the consented participants get DOT measurements taken before 7 days of life; (iii) for 80% of the consented participants, parent-reported developmental assessment is available at 6 and 12 months; (iv) Time required for resting-state data acquisition per infant < 45 min.	Descriptive statistics (mean and SD) for continuous variables. Proportions for dichotomous variables.
To assess the fidelity and safety of DOT measurements in neonates.	Adverse reactions, adequate measurements, and time for data acquisition.	(i) Reporting any adverse skin reactions to sensors or excessive agitation in the neonate requiring early termination of the study. (ii) Data quality will be assessed by recording the degree of the signal-to-noise ratio.	Qualitative analysis.
To identify logistic challenges, unexpected adverse effects, or technical difficulties.	Adverse events or operational difficulties.	An adequate amount of time and number of personnel required for each stage of the study and staff workload. Lack of logistic challenges.	Qualitative reporting.
To gain stakeholder engagement, including from parents and NICU nurses.	Engagement level.	Positive perceptions about the study procedures from parents and nurses.	Qualitative survey analysis.

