DOT-based functional neuroimaging may provide early recognition of neural deficits at the bedside after several perinatal events such as premature birth, intraventricular hemorrhage, and birth trauma. This tool can be used to analyze the effects of bedside interventions and individualized care plans, such as music therapy, reading programs, sensory modulation techniques, and sleep, on the functional maturation of the developing brain. This study aims to conduct a single-center pilot project to assess the feasibility of a larger-scale study investigating the prognostic value of neonatal brain functional connectivity measures using DOT to predict long-term neurological outcomes. The primary objectives of this pilot study are to (i) demonstrate the feasibility of recruitment and retention strategies along with data collection methods in the NICU and (ii) assess the fidelity and safety of DOT measurements in neonates. The secondary objectives of this pilot study include (i) identifying logistic challenges, unexpected adverse effects, or technical difficulties, (ii) gaining stakeholder engagement, including parents and NICU nurses, and (iii) providing preliminary data on the variability of outcome measures to calculate the sample size of the larger trial accurately.

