### 2.8. Objectives and Outcomes

#### Objectives and Corresponding Outcomes of the Feasibility Trial

Objective 1: To determine the feasibility of recruitment and retention strategies and data collection methods in the NICU. Feasibility will be assessed by reporting the following metrics: (i) The recruitment rate will be reported to assess the ability to recruit the target population within the desired timeframe, determined by the number of eligible participants who are enrolled in the study. We will maintain a recruitment tracking log. (ii) The follow-up rate will be used to assess the ability to retain participants and complete follow-up assessments, as determined by the percentage of enrolled patients who complete follow-up at 12 months. We will maintain a record of participant follow-up procedures and dropout rates. (iii) The rate of missing data will be determined by the percentage of completed data fields measured by reviewing collected data to identify any missing information, inconsistencies, or incomplete responses. *Criteria for Feasibility:* The main study will be feasible if the pilot study is successful based on the predefined criteria: (i) 80% of the eligible patients consent to the testing; (ii) 90% of the consented participants get DOT measurements taken before 7 days of life; (iii) for 80% of the consented participants, parent-reported developmental assessment is available at 6 and 12 months.

Objective 2: To assess the fidelity and safety of DOT measurements in neonates. (i) Safety will be assessed by reporting any adverse skin reactions to sensors or excessive agitation in the neonate, requiring early termination of the study. (ii) Data quality will be assessed by recording the degree of the signal-to-noise ratio. We will keep a record of the ability to properly place sensors with good contact and the ability to minimize motion artifacts and ambient light interference in each subject. (iii) Ability to complete adequate data acquisition within 45 min. *Criteria for Feasibility:* Time required for resting-state data acquisition per infant < 45 min.

Objective 3: To identify logistic challenges, unexpected adverse effects, or technical difficulties. Operational feasibility will be assessed based on the time and personnel required for each stage of the study, as well as the logistical challenges.

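### The Table 1 success criterion for the primary safety aim is a reporting procedure analysed qualitatively, so as written it is met at any number of adverse events

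*Protocol article*

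**What the plan says.** The Introduction makes it primary objective (ii) to "assess the fidelity and safety of DOT measurements in neonates".

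Table 1, Primary Aims, has a column for success criteria and a column for method of analysis. In the fidelity-and-safety row the first holds two entries: "Reporting any adverse skin reactions to sensors or excessive agitation in the neonate requiring early termination of the study" and "Data quality will be assessed by recording the degree of the signal-to-noise ratio". The second reads "Qualitative analysis". The recruitment-and-retention row above has numerical criteria, and its method includes "Proportions for dichotomous variables".

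In section 2.8, Objective 2, almost the same text describes assessment: "Safety will be assessed by reporting any adverse skin reactions to sensors or excessive agitation in the neonate, requiring early termination of the study". The separately labelled criterion there is "Time required for resting-state data acquisition per infant < 45 min". Table 1 places that time criterion in the recruitment row instead.

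Section 2.8, Objective 1, states how the pilot is to be judged: "The main study will be feasible if the pilot study is successful based on the predefined criteria". The criteria that follow concern consent, DOT measurement before 7 days of life, and availability of the 6- and 12-month questionnaires.

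**The concern.** A success criterion should be capable of failing. The safety entry names something the team will do rather than a level of tolerability to be observed, so the number of infants affected has no bearing on whether it is met.

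The analysis method adds to the problem. A skin reaction or a session stopped early is a yes/no event for each infant, the kind of variable for which the row above plans proportions. A qualitative account has no stated numerator, denominator or interval, so a reader could not tell what 25 infants can and cannot exclude.

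At stake is how the safety result carries forward. The device is investigational and the infants have encephalopathy. Section 2.7.1 expects skin irritation to be unlikely but gives no rate. The pilot is where a rate, with its uncertainty, could be obtained for planning the larger study.

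**Working it through.** **Step 1. Can any printed criterion register harm directly?**

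| Place | Criterion | Does an adverse event change it? |
|---|---|---|
| Table 1, recruitment and retention | Consent, DOT timing, questionnaires, acquisition time | No limit on events |
| Table 1, fidelity and safety | Reporting events; recording signal-to-noise ratio | No; met by reporting and recording |
| Table 1, logistic challenges and unexpected adverse effects | Time, personnel, workload, logistics | Events are an outcome, but the criterion does not mention them |
| Table 1, stakeholder engagement | Favourable views of parents and nurses | Indirectly, with no number |
| Section 2.8, Objective 1 | Consent, DOT timing, questionnaires | No limit on events |
| Section 2.8, Objective 2 | Acquisition time under 45 min | No; see below |

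The time criterion does not stand in for safety. Section 2.7.1 already caps optode placement at 45 min, and a session cut short for agitation also lasts less than 45 min.

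So the safety entry is met for every count from 0/25 to 25/25, and no other printed criterion sets a limit on skin reactions or stopped sessions.

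**Step 2. What would a count in 25 infants tell us?**

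Inputs: n = 25 (section 2.10, chosen on practical grounds with no rate, precision or power behind it, so there is no planned figure to reproduce). The 95% level and the true rates below are assumptions made here; the article states neither.

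Exact upper limit for 0 events in n:
- Two-sided 95%: 1 − 0.025^(1/25) = 0.137, or 13.7%.
- One-sided 95%: 1 − 0.05^(1/25) = 0.113, or 11.3%.
- If only 20 infants were measured (illustrative), two-sided: 1 − 0.025^(1/20) = 0.168, or 16.8%.

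Chance of seeing no event in 25, (1 − p)^25:
- p = 2%: 0.98^25 = 0.60.
- p = 5%: 0.95^25 = 0.28.
- p = 10%: 0.90^25 = 0.07.

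Exact (Clopper-Pearson) two-sided 95% intervals for small non-zero counts:
- 1/25 = 4% (0.1% to 20.4%).
- 2/25 = 8% (1.0% to 26.0%).
- 3/25 = 12% (2.5% to 31.2%).

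These figures show what a count with an interval would convey and a narrative would not. They do not show that 25 is the wrong size for a feasibility pilot.

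**The case against.** **Descriptive safety reporting is acceptable in a pilot of 25.** This stands. Section 2.8 separates how safety is assessed from the labelled criterion, and Table 1 is a summary into whose success column the assessment text has been moved. The firm defects are therefore the misplaced entry and the method printed beside it. A go/no-go limit on harm is one cure, not the only one.

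**A reader might infer that harm cannot affect any conclusion of the pilot.** The article does not support that. The stakeholder criterion in Table 1 depends on favourable perceptions, and the survey under Objective 4 asks parents and nurses about infant discomfort. Objective 2 also lists the ability to complete adequate acquisition, which sessions ended for agitation would reduce. These routes are indirect and carry no number, but they exist.

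**A reader might also infer that the authors would treat zero events as proof of safety.** Nothing in the article says so. The 13.7% limit guides the wording of a conclusion; it does not rebut one already drawn.

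**Nor does the 90% criterion imply a safety denominator of 23.** It concerns measurement before 7 days of life, while Table 2 places DOT at 4–15 days, so an infant who misses the 7-day target might still be measured.

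**Context on risk.** The device is non-invasive and authorised by Health Canada for this study, the ethics board has approved the study, and earlier safety assessments in neonates are cited. This lowers the likely event rate but does not make the criterion informative.

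**Interval methods are often left to an analysis plan.** That is fair for detail. Here, however, the article prints a method for a primary aim, and it is one that does not suit yes/no events.

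**Conclusion.** The concern holds in a limited form. The printed success criterion for the safety part of a primary aim cannot fail, and the printed method gives no count or proportion. The only criterion that section 2.8 attaches to the same objective is a recording time that does not measure harm. This follows from the wording alone and needs no assumption.

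The size is illustrative and rests on an assumed 95% level with all 25 infants measured: a clean 0/25 would exclude only rates above 13.7% two-sided (11.3% one-sided), and at a true rate of 5% about 28% of such pilots would see no event.

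This is a correctable fault in the table and analysis wording. It does not invalidate the pilot or its sample size, and it does not by itself require a progression limit on safety.

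**What to change.** 1. In Table 1, replace the qualitative method for the safety items with two results: the number and proportion of measured infants with a skin reaction, and the number and proportion whose session was stopped early for agitation. Give each an exact 95% confidence interval. Keep free-text description as a supplement.
2. Define the denominator as infants in whom a recording was attempted, so that stopped sessions stay in. State whether a skin reaction counts only if it ended the session, since the present sentence can be read either way.
3. Limit the safety conclusion to what the upper confidence limit excludes.
4. Choose one of two courses for the success column. Either move the reporting text out of it and label safety as descriptive only, or have the sponsor set its own maximum before the first recording and add it to the criteria in section 2.8. No value is suggested here; the article gives no acceptable rate from which to derive one.
5. In the same edit, reconcile the place of the time criterion (Objective 2 in section 2.8, recruitment row in Table 1), and treat the signal-to-noise entry in the same way, since it too names a procedure with no level.

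The cost is table and protocol wording, with no extra infants or procedures. The safety statement becomes more modest and, if a limit is set, the pilot gains a criterion that it can miss.

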**Secondary Aims**			
**Objectives**	**Outcome**	**Hypothesis**	**Analysis**
To explore the differences in brain metrics between male–female, mild–moderate–severe encephalopathy groups.	Brain metrics.	Significant difference in regional brain metrics.	Student *t*-test.
To explore the correlation of severity of brain injury score with brain metrics.	MRI injury score.	We can determine the required sample size for a definitive trial.	Regression analysis.
Correlation of brain metrics with neurological outcome.	ASQ scores at 6 months and 12 months.	We can determine the required sample size for a definitive trial.	Regression analysis.

**Table 2 neurosci-06-00060-t002:** Participant timeline.

	Study Period								
	Enrollment	Allocation	Post-Allocation						Close Out
Timepoint		Day 0	1–3 days	4–7 days	4–15 days	NICU discharge	6 months	12 months	
Screening for eligibility	X								
Approaching parents for informed consent	X								
Study ID created	X								
Allocation	X								
Clinical data collection	X	X	X	X	X	X			
Therapeutic hypothermia			X						
EEG monitoring			X						
MRI brain				X					
DOT measurement					X				
ASQ-3							X	X	
ASQ: SE-2							X	X	

Abbreviations: ASQ-3, Ages and Stages Questionnaire-3rd version; ASQ: SE-2 Ages and Stages Questionnaire: Socio-emotional-2nd version; MRI, magnetic resonance imaging; DOT, diffuse optical tomography; EEG, electroencephalogram.

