### 2.2. Study Setting

This study will be conducted at the McMaster Children’s Hospital neonatal intensive care unit (NICU). The province of Ontario, Canada’s perinatal services are organized into three levels, namely the following: (i) Level 1: low neonatal risk, postnatal care of healthy newborn and resuscitation/stabilization of ill infants before transfer; (ii) Level 2: neonatal care for gestational age > 32 weeks and birth weight > 1500 g [exception: Level 2c > 30 weeks and >1200 g]; and (iii) Level 3: neonatal intensive care for any gestational age and birth weight, availability of subspecialty consultants, and surgical capability. Since therapeutic hypothermia resources are available solely in Level 3 hospitals in Ontario, Canada, neonates born across Level 1 and 2 hospitals are transferred to Level 3 with a specialized neonatal transport team [www.pcmch.on.ca, 2 June 2025]. McMaster Children’s Hospital is a Level 3 unit attached to a high-risk maternal and fetal medicine unit. Approximately 50–60 neonates per year are admitted to the NICU with the diagnosis of HIE; ~90% of them receive therapeutic hypothermia, and ~80% of them are outborn neonates. Outborn neonates may be born in any of the surrounding Level 1 or Level 2 hospitals in the catchment area of McMaster Children’s Hospital. When indicated, passive cooling is started in the referring hospital, and the neonate is transferred immediately to the Level 3 unit to receive hypothermia therapy using a servo-controlled device. A two-member in-house neonatal transport team facilitates the transfer of neonates from the referring center to the Level 3 NICU.

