### 2.3. Therapeutic Hypothermia Protocol

Therapeutic hypothermia is the standard of care for moderate to severe HIE. The severity of encephalopathy is graded using a modified Sarnat Staging [34] based on 6 domains: level of consciousness, spontaneous activity, posture, tone, primitive reflexes (suck and Moros’ reflex), and autonomic nervous system (heart rate, pupils, and respiratory effort). At McMaster Children’s Hospital, a servo-controlled device, CritiCool^®^, Belmont Medical Technologies Ltd., Billerica, MA, USA, is used for neonatal hypothermia therapy. The infant is wrapped in a temperature-regulated cooling blanket to reduce core body temperature to 33–34 °C and maintained for 72 h using a rectal temperature probe for continuous monitoring. Then, the neonates are rewarmed to 36.5–37.5 °C over 6 h. Electrolyte levels, fluid balance, bleeding tendency, and cardiorespiratory functions are closely monitored during the therapy. Additionally, brain function is routinely monitored with continuous amplitude-integrated EEG or continuous video EEG until rewarming is completed to detect and manage seizures. All neonates will undergo structural brain MRI and MR spectroscopy on a 1.5 Tesla MRI scanner (Siemens Healthcare Limited, Forchheim Germany) at a median age of 3–5 days. MRIs conducted in the clinical setting include sequences T1W, T2W, DWI, SWI, and, if indicated, MRV/MRA. After discharge, all infants are followed in the Developmental Follow-Up clinic for 2–3 years to detect and treat developmental delays.

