### 2.10. Sample Size and Recruitment

The National Center for Complementary and Integrative Health notes that sample size should be based on practical considerations, including participant flow, budgetary constraints, and the number of participants needed to reasonably evaluate feasibility goals [47]. Hence, for this work, a sample size of 25 was considered adequate to reach saturation and establish feasibility. If the feasibility criteria are met, the sample size for the larger trial will be determined based on the data analysis.

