After preprocessing, resting-state functional connectivity and network analyses will be conducted using NIRS_KIT [50] and the Graph Theoretical Network Analysis Toolbox (GRETNA) [51], both of which are MATLAB-based open-sourced toolboxes. Pearson correlation coefficients will be calculated between all pairs of channels and among channels within specific ROIs. GRETNA will then analyze these correlation coefficients to characterize the topology of both whole-brain and ROI-specific networks. To investigate disruptions in specific neural networks, we will focus on the functional connectivity of the default mode, sensorimotor, auditory, and visual networks. These networks will be identified by co-registering the fNIRS recording channels to the standard MNI space using STORM-Net [52], a Python-based photogrammetry application (Version 3.13). We will then calculate global network metrics including **assortativity** (the tendency of nodes to connect with other nodes of similar degree), **hierarchy** (the degree of hierarchical organization), **small-worldness** (the ratio between local clustering and global integration), **global efficiency** (the efficiency of parallel information transfer), **local efficiency** (the network’s fault tolerance), and **synchronization** (the degree of correlated activity among nodes) [53]. These metrics provide insights into communication efficiency, information processing speed, network resilience, and overall connectivity. We hypothesize that hypoxic–ischemic injury will alter these network metrics, specifically manifesting as weaker interhemispheric connectivity and stronger intrahemispheric connectivity, which may represent compensatory adaptations during recovery.

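### Table 1 names Student's t-test for a comparison that includes three encephalopathy severity groups; the test fits the sex comparison but cannot test a three-level factor

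*Protocol article*

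**What the plan says.** In Table 1 of the protocol article, under Secondary Aims, a single row covers two comparisons: "To explore the differences in brain metrics between male–female, mild–moderate–severe encephalopathy groups". The outcome is brain metrics, the hypothesis is "Significant difference in regional brain metrics", and the analysis column contains only "Student *t*-test". The article states no three-group test, trend test, pooling of stages or rule for multiple comparisons.

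The next two rows, on the MRI injury score and the ASQ scores, are assigned "Regression analysis". Severity is graded by modified Sarnat staging (sections 2.3 and 2.11). On size, section 2.10 says "a sample size of 25 was considered adequate to reach saturation and establish feasibility"; it gives no significance level, power or effect size for this comparison.

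**The concern.** A two-sample t-test compares two means, and the severity factor has three ordered levels. The named method therefore cannot answer the severity half of the aim as written. An analyst would have to improvise: run all three pairs without adjustment, pick one pair, or merge stages. The row supports none of these choices over the others, and they can give different answers.

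The hypothesis adds to the difficulty because it asks for significance rather than for an estimate. Three unadjusted chances per metric to reach p < 0.05 raise the false-positive rate, and pairwise testing makes no use of the order mild, moderate, severe. At stake is how far reported severity differences in brain metrics can be trusted. The feasibility conclusions are not affected.

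**Working it through.** **Plan's own figure.** There is none to reproduce. The article gives N = 25 on practical grounds and no operating characteristics for this row.

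**Inputs from the article.** N = 25 (section 2.10); three severity levels, two sexes and Student's t-test as the only method (Table 1).

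**Assumptions, not in the article.** Two-sided 5% level, 80% power where power is used, normal data with equal means under the null, and severity splits as shown below. The article gives no severity distribution, so four splits were tried.

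**Step 1: number of tests.** Three groups give 3 × 2 / 2 = 3 pairs per metric.

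**Step 2: simple error rate.** If the three tests were independent, the chance of at least one false positive would be 1 − 0.95³ = 14.3%. They share groups, so the true figure is somewhat lower.

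**Step 3: simulation (100,000 runs per split).**

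| Assumed split (three stages) | Any of 3 pairwise t-tests p < 0.05 | One-way F test p < 0.05 |
|---|---|---|
| 8 / 9 / 8 | 12.2% | 4.9% |
| 5 / 15 / 5 | 12.2% | 4.9% |
| 3 / 17 / 5 | 12.4% | 5.1% |
| 10 / 12 / 3 | 12.3% | 5.0% |

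Each pairwise test alone holds its level (4.9–5.1%). The inflation comes from running three, and it hardly depends on the split.

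**Step 4: what N = 25 could detect.** At 80% power:
- sex, 12 v 13: a standardised difference of 1.17;
- two stages, 8 v 8: 1.51, or 1.81 with a Bonferroni correction for three pairs;
- one three-group F test: Cohen's f of 0.67.

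All are large effects, so a significance hypothesis suits these data poorly whichever test is used. Estimates with intervals are more informative.

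**Step 5: feasibility of the replacement.** A model with a three-level stage factor leaves 25 − 3 = 22 residual degrees of freedom and uses all infants to estimate the variance. An 8 v 8 t-test has 8 + 8 − 2 = 14. Adding sex and age at scan to the three-level model would leave 20.

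**The case against.** The strongest reply is one of proportion. This is an exploratory secondary aim in a 25-infant feasibility study. No success criterion uses the test, and section 4 already warns that the small sample may mislead about associations. The article is also a condensed account, and a fuller plan might merge stages or specify a three-group test.

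The argument about proportion stands and limits the weight of the point. The argument about condensation does not remove it. The article has not left the method open: it names one, and that method does not fit the aim beside it. If merging stages were intended, the row would describe a two-group comparison.

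A reader might infer four stronger things that the article does not support.

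- **Sex is ignored.** It is not. Sex is one of the two factors compared in the same row, and the t-test suits it.
- **The severity comparison is confounded by maturity.** Gestational age from 35 weeks upward allows variation, but nothing in the article shows that maturity differs by stage, and a covariate list is commonly left to the full plan. The DOT timing (within or before 7 days in the Abstract and section 2.8, apparently 4–15 days in Table 2) is a separate matter to reconcile.
- **Hundreds of tests are planned.** Six global metrics × five network levels (whole brain plus four) × three haemoglobin contrasts × four comparisons is 6 × 5 × 3 × 4 = 360 tests, hence 360 × 0.05 = 18 expected false positives if every null were true. Section 3 says only "we will focus on the functional connectivity of the default mode, sensorimotor, auditory, and visual networks". The three contrasts appear in section 2.7.4 for seed-based correlation maps. No section says that every combination will be tested.
- **The mild group will hold two or three infants.** This takes "90% of them receive therapeutic hypothermia" together with "Therapeutic hypothermia is the standard of care for moderate to severe HIE", treats uncooled as mild, and computes 10% of 25 = 2.5. Neither section says that mild cases are never cooled or gives a severity distribution.

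**Conclusion.** The point holds in a narrow form. Table 1 assigns a two-group test to a comparison that includes three severity groups. Taken literally as three unadjusted pairwise tests, it gives about a 12% chance of a false positive per metric instead of 5%, and it ignores the order of the Sarnat stages. The 12% assumes normal data, equal means and a 5% level for each test. It was stable over the four splits tried.

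The weight is minor to moderate: the analysis is exploratory, and N = 25 and the feasibility criteria do not rest on it. The t-test for sex is sound. The lack of adjustment for age at scan is not an error in this article.

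**What to change.** In Table 1, Secondary Aims, separate the two comparisons:

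- **Sex:** keep Student's t-test.
- **Severity:** name one analysis that takes all three stages together, either one-way ANOVA or a linear model with Sarnat stage as the factor.
- **Reporting:** give differences in brain metrics with 95% confidence intervals for both comparisons.
- **Hypothesis:** replace the expectation of a significant difference with a statement that differences by sex and stage will be estimated and are exploratory.

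Either form of severity analysis corrects the mismatch, and the choice is the authors'. One-way ANOVA assumes no pattern but does not use the ordering. An ordered stage term uses it, at the price of assuming a steady trend if scored with equal spacing. Adjusting the model for age at scan is optional.

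The cost is a change of analysis wording and fewer p-values. No new data, visits or participants are needed.
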